##### Health-care re-orientation

Health-care re-orientation will be extracted from the CM intervention medical records at 12 months. Health-care reorientation at 12 months will be used as outcome.

##### Quality of life

We will use the World Health Organization’s WHOQOL-BREF [42] to evaluate quality of life at baseline, 3-, 6- and 12-month follow-up.

##### Empowerment and self-efficacy

We will evaluate empowerment and self-efficacy at baseline, 3-, 6- and 12 months, with the Health Care Empowerment Informed, Committed, Collaborative and Engaged subscales of the Health Care Empowerment Inventory [17] and Self-Efficacy with the Self-Efficacy Scale [43].

##### Health literacy

Similarly, we will assess health literacy at baseline, 3-, 6- and 12 months using the European Health Literacy Project Questionnaire (HLS-EU-16) [44].

##### Problematic alcohol use and precursors of alcohol use changes

We will measure problematic alcohol use with the AUDIT-C [45]. In addition, we will examine precursors of alcohol use changes (among participants scoring ≥4 for males and ≥ 3 for females at the AUDIT-C) with four single-item visual analog rulers assessing importance, intentions, readiness and confidence regarding alcohol use changes developed by Walton and colleagues [46]. These measures will be assessed at baseline, 3-, 6-, and 12-months.

### Data analysis plan

#### Implementation measures analysis

Descriptive statistics will be used to describe participants’ characteristics and to report implementation outcomes. We will also test implementation measures changes over time. Given that we will have a small sample size regarding implementation outcomes, these analyses will be triangulated with the qualitative data. Specifically, interview contents will be transcribed and explored to identify participants’ recurring codes and categories; we will use conventional content analysis (i.e., a systematic process of coding and classification) [47] using a qualitative software (i.e., Atlas.ti or NVivo) to examine qualitative data.

#### Clinical outcomes

Data will be screened for missing cases, outliers, and normality of distributions using descriptive statistics and plots. We will take appropriate steps to deal with missing data. First, we will conduct analyses to detect missingness patterns and test whether they may be considered “ignorable.” [48] If more than 5% of outcome data are missing, [49] we will divide the sample into 2 groups (i.e., missing, not missing), and use fully observed variables to predict missingness on the affected outcome. If fully observed variables are not significant predictors, missingness may be considered as “observed at random” and fulfilling some criteria for “missing completely at random” (MCAR) assumptions. In that case, we will use multiple imputations procedures for measured outcomes and direct maximum likelihood estimation for structural models. If data missingness is non ignorable (MNAR), we will use pattern-mixture models with multiple imputation to model the missingness mechanism.

Main analyses will comprise multilevel models (i.e., MLM; mixed effects model) [50] utilizing appropriate distributions for the outcome variables (e.g., Poisson, negative binomial, normal). MLM examine the effect of time (after receiving the CM intervention) on clinical outcomes (e.g., quality of life, self-efficacy). MLM is appropriate to handle nonindependence data. Specifically, data will be clustered by participants (i.e., repeated measures) and by hospitals. MLM does not assume independence of observations. Dependence is modeled through random effects (representing different sources of variability in the data). We will include sources of random variability at the group level accounting for between-group differences and another random effects for the individual accounting for within-person differences in the repeated measures. MLM will be adjusted for demographic variables (i.e., age and gender), ED use, at-risk behaviors (e.g., alcohol use disorders) and health status. Descriptive statistics will be conducted on SPSS and MLM on STATA. The significance level will be set at *p* = .05.

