### Limitations

There are several expected limitations in this current research project that were carefully considered while designing the study. Regarding clinical outcomes, the design of this study allows patients’ evolution to be evaluated after receiving the CM intervention (i.e., pre-post intervention; within-subjects design) in the sites implementing the intervention. A well-known limitation related to this design is regression to the mean. In fact, we previously conducted research using gold-standard randomized controlled trial to test the CM intervention efficacy [3] and the proposed within-subjects’ design is consistent with Stages I and II treatment development [51]. That said, interpretation of pre-post intervention changes on health outcomes will be made with caution. Next, self-reported data can be subject to reporting bias [52, 53]. It can however, be reliable when measures are developed for and piloted on the target population, timeframes are manageable, confidentiality is ensured and the target behavior is not stigmatized [54, 55]. The above conditions were carefully considered when designing the study, thereby minimizing the risk of self-report bias. Furthermore, recruitment and retention can be a challenge with the target population (i.e., FUEDs), resulting in missing data. However, previous work with a similar population, has demonstrated the possibility to attain acceptable 1-year retention rates [3]. Procedures for maximizing study retention will therefore be inspired from the latter study. For instance, we will use incentives to help retention over time (gift cards of increased value for each follow-up assessment completed: 10, 20 and 20 CHF for 3, 6 and 12-month follow-up assessment). Additionally, specific steps will be taken to address any bias that may occur because of missing data as described previously. Finally, although not known at this stage, the patient sample size will be larger than the hospital sample size; therefore, the implementation outcomes analyses will not have the same level of analysis and will mostly remain descriptive. To address this limitation, we will use mixed methods (i.e., qualitative and quantitative methods) to assess the implementation process and outcomes.

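### A significance test on observed variables picks the missing-data method: the missing-at-random case has no stated action, and pattern-mixture modelling waits on a condition the test cannot detect

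*Protocol article*

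**What the plan says.** The rule is in the protocol article, Data analysis plan, Clinical outcomes. Its declared purpose is to test whether missingness is ignorable. It runs as follows.

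- Trigger: "If more than 5% of outcome data are missing".
- Test: split the sample into missing and not missing, and "use fully observed variables to predict missingness on the affected outcome".
- Non-significant result: "If fully observed variables are not significant predictors, missingness may be considered as “observed at random” and fulfilling some criteria for" (the sentence ends by naming MCAR, that is, missingness completely at random). The action is: "In that case, we will use multiple imputations procedures for measured outcomes and direct maximum likelihood estimation for structural models".
- Remaining branch: "If data missingness is non ignorable (MNAR), we will use pattern-mixture models with multiple imputation to model the missingness mechanism".

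The section does not mention missing at random, gives no action for a significant result, and gives no criterion for declaring MNAR. The same section makes mixed-effects models the main analysis, adjusted for age, gender, ED use, at-risk behaviours and health status, with significance at 0.05. The Limitations section anticipates missing data in this population and relies on the rule: "specific steps will be taken to address any bias that may occur because of missing data as described previously".

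**The concern.** Ignorable missingness covers both MCAR and MAR. When observed variables predict missingness, the data are compatible with MAR, and imputation or likelihood methods that use those variables then remove bias. The plan ties these methods to the opposite result, where they are least needed to remove bias, and leaves the MAR-compatible result without an action.

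MNAR means that missingness depends on the unseen value after allowing for what was seen. A regression of missingness on observed variables cannot establish or exclude that. The pattern-mixture analysis therefore depends on a condition that the plan cannot evaluate. The test result also depends on sample size, which the Participants section says is not known.

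The clinical part is an uncontrolled pre-post comparison whose main model estimates the effect of time. No control arm offsets attrition, so bias in a follow-up mean passes directly into the estimated change. Quality of life is a main outcome and is collected by telephone interview at 3, 6 and 12 months. It and the secondary questionnaire outcomes are the most exposed.

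**Working it through.** **Logic of the rule**

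| Result of the stated test | Mechanisms compatible with it | Action stated |
|---|---|---|
| Non-significant | MCAR, MAR with low power, MNAR | Multiple imputation or maximum likelihood |
| Significant | MAR, MNAR, or a chance finding under MCAR | None |
| Cannot be reached by this test | MNAR declared | Pattern-mixture models |

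With several predictors each tested at 0.05, a chance finding under MCAR is not rare. For *k* independent predictors the probability of at least one is 1 − 0.95^*k*: 18.5% for *k* = 4 and 33.7% for *k* = 8.

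**Illustrative simulation**

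The article gives no figure to reproduce. All inputs below are assumed except the 0.05 level, which is the plan's (taken as two-sided).

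- Baseline *X* and follow-up *Y* in SD units, true change zero, *Y* = ρ*X* + √(1 − ρ²)·ε.
- logit P(missing) = *a* − ln(OR)·*D*, with *D* = *X* for MAR and *D* = *Y* for MNAR; *a* set to give 30% missing. Lower values are more often missing.
- OR 1.5 or 2.0 per SD; n = 100, 200 and 400; 1,500 runs per cell.
- Test: logistic regression of missingness on *X*.
- MAR-based estimate: regress *Y* on *X* among those observed, then average the predictions over everyone.

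| Truth | ρ | OR | Test non-significant, n = 100 / 200 / 400 | Bias of MAR-based mean (SD) |
|---|---|---|---|---|
| MCAR | 0.5 | – | 96% / 96% / 96% | up to 0.002 |
| MAR | 0.5 | 1.5 | 57% / 27% / 6% | within 0.002 |
| MAR | 0.5 | 2.0 | 17% / 1% / 0% | within 0.002 |
| MNAR | 0 | 1.5 | 95% / 96% / 96% | 0.12 |
| MNAR | 0 | 2.0 | 96% / 95% / 94% | 0.19 |
| MNAR | 0.3 | 1.5 | 92% / 88% / 80% | 0.11 |
| MNAR | 0.3 | 2.0 | 86% / 75% / 57% | 0.17 to 0.18 |
| MNAR | 0.5 | 1.5 | 87% / 78% / 56% | 0.09 |
| MNAR | 0.5 | 2.0 | 72% / 48% / 17% | 0.15 |

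**Hand check of the MNAR bias.** With ρ = 0 it is roughly 0.3 × ln(OR): 0.3 × 0.405 = 0.12, and 0.3 × 0.693 = 0.21 (simulated 0.19; the approximation runs slightly high). Using the baseline multiplies the bias by about 1 − ρ². For ρ = 0.5 that gives 0.75 × 0.12 = 0.09 and 0.75 × 0.19 = 0.14, close to the simulated 0.09 and 0.15.

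**What the table shows**

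1. Under MAR the same mechanism is non-significant in 57% of runs at n = 100 and 6% at n = 400, so sample size decides the branch. The MAR-based estimate is nearly unbiased throughout, against 0.06 to 0.10 SD for complete cases. Nothing is gained by making its use depend on the test.
2. Under MNAR with no baseline correlation, the test behaves as it does under MCAR at every n.
3. Passing the test does not mark out the safer datasets. For MNAR with ρ = 0.5, OR 2.0 and n = 200, the bias is 0.147 SD over all runs and 0.147 SD in the non-significant runs alone.

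**The case against.** Much can be said for the plan.

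- **A reader might infer that it takes non-significance as proof of MCAR.** It does not. The wording is hedged and speaks of meeting only some of the criteria. What stands is that a non-significant result is enough to decide the branch.
- **A wrong MCAR label does little harm when the truth is MAR.** Multiple imputation and maximum likelihood do not need MCAR, and the rule names no complete-case fallback. This stands. The harm in that branch is confined to MNAR data that receive no sensitivity analysis.
- **A reader might infer that a significant result sends MAR data to the MNAR branch, so that a valid method is abandoned.** That requires the two branches to be exhaustive, which the text does not say. MAR is ignorable on the plan's own terms and need not trigger pattern-mixture models. The text supports only that the action is undefined.
- **The main mixed model already adjusts for several baseline variables and is not explicitly conditional on the test.** This stands and makes the correction smaller. It does not settle what to do with other predictors of dropout, and it gives no MNAR assessment.
- **ED visits, the other main outcome, come from medical records.** Missed interviews do not directly create missing ED data, so the scope is narrower than all outcomes.
- **The article is condensed, and it promises caution in interpreting pre-post changes.** Condensation would excuse an absent detail. Here the trigger, the test, the conditions and the actions are all written down, and the rule they form is defective.

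**Conclusion.** The concern holds in a limited form. The rule lets a significance test select the method, gives no action for the MAR-compatible result, and puts the MNAR analysis behind a condition that its only test cannot detect. These defects follow from the text and need no simulation.

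The size is not known. Under the assumed inputs, with baseline correlation 0.3 to 0.5, MNAR data gave a non-significant test in 17% to 92% of runs, and a MAR-based mean was biased by 0.09 to 0.18 SD. With no baseline correlation the figures are 94% to 96% and 0.12 to 0.19 SD. In the direction simulated, with worse-off patients lost, the bias looks like improvement where there is none. A larger sample raises the chance of a significant result when baseline and follow-up are correlated, but such a result still cannot separate MAR from MNAR.

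The figures do not show that this trial's data will be MNAR, or that the planned analysis will be biased by any given amount. The concern applies mainly to quality of life and the secondary questionnaire outcomes.

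**What to change.** Replace the branching paragraph with three statements.

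1. The primary analysis of each questionnaire outcome is the mixed model (or multiple imputation) under MAR, using all available records and including baseline variables that predict dropout. It applies whatever the missingness test shows and however much is missing.
2. A pattern-mixture or delta-shift sensitivity analysis is always reported for 12-month quality of life, for example by worsening the imputed values step by step until the conclusion changes.
3. The comparison of participants with and without missing outcomes is kept, as description only.

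The plan already names mixed models, multiple imputation and pattern-mixture models. The cost is a rewritten paragraph and one additional sensitivity analysis, with no change to data collection.

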## Discussion

This paper describes the protocol of a research project aiming to implement a CM intervention tailored to FUEDs in hospitals in the French-speaking region of Switzerland, using a hybrid design that allows evaluating both implementation and clinical outcomes [27].

### Significance

This project addresses a critical area of ED health services overuse using a practical solution, while taking an innovative research approach that will contribute to the growing literature on this topic. In terms of research feasibility and innovation, implementation science is an emerging field and serves as an ideal theoretical foundation to complement the study of the key clinical outcomes in diverse settings. The hybrid study design, and rooting our project in the established GIF and Re-AIM frameworks, provides a novel and feasible research approach. Findings of the current research project will provide useful information related to the mechanisms and processes for implementing a CM intervention for FUEDs into broader practice in the real-world settings.

This research project is also likely to have social and economic implications. ED overuse and overcrowding is a critical problem, and this project promotes a potential solution. At the Lausanne University Hospital ED, FUEDs accounted for 4.4% of ED patients yet 12.1% of all ED visits (i.e., in 2008–2009; *n* = 5813) [4]. There is a strong link between chronic disease and frequent ED use, driven largely by the medical and social complexity of these patients. Addressing ED overuse through CM redirects FUEDs to more appropriate forms of care, including primary care or substance abuse treatment, while remaining cost-effective. By developing a CM intervention program and studying its implementation at multiple sites throughout the French-speaking region of Switzerland, this project will provide insights and lessons for the broader use of CM interventions for health care services overuse throughout Switzerland.

Finally, the CM intervention targets a defined population— FUEDs —that is frequently highly vulnerable in terms of medical complexity, suffering from multiple chronic medical conditions, mental health and substance abuse treatment needs, as well as modifiable social determinants of health, including homelessness or low household income. Therefore, this project also addresses a medically and socially complex patient population with chronic health care and social service needs, as well as emphasizing improved communication and care coordination within interdisciplinary care teams.

### Limitations

There are several expected limitations in this current research project that were carefully considered while designing the study. Regarding clinical outcomes, the design of this study allows patients’ evolution to be evaluated after receiving the CM intervention (i.e., pre-post intervention; within-subjects design) in the sites implementing the intervention. A well-known limitation related to this design is regression to the mean. In fact, we previously conducted research using gold-standard randomized controlled trial to test the CM intervention efficacy [3] and the proposed within-subjects’ design is consistent with Stages I and II treatment development [51]. That said, interpretation of pre-post intervention changes on health outcomes will be made with caution. Next, self-reported data can be subject to reporting bias [52, 53]. It can however, be reliable when measures are developed for and piloted on the target population, timeframes are manageable, confidentiality is ensured and the target behavior is not stigmatized [54, 55]. The above conditions were carefully considered when designing the study, thereby minimizing the risk of self-report bias. Furthermore, recruitment and retention can be a challenge with the target population (i.e., FUEDs), resulting in missing data. However, previous work with a similar population, has demonstrated the possibility to attain acceptable 1-year retention rates [3]. Procedures for maximizing study retention will therefore be inspired from the latter study. For instance, we will use incentives to help retention over time (gift cards of increased value for each follow-up assessment completed: 10, 20 and 20 CHF for 3, 6 and 12-month follow-up assessment). Additionally, specific steps will be taken to address any bias that may occur because of missing data as described previously. Finally, although not known at this stage, the patient sample size will be larger than the hospital sample size; therefore, the implementation outcomes analyses will not have the same level of analysis and will mostly remain descriptive. To address this limitation, we will use mixed methods (i.e., qualitative and quantitative methods) to assess the implementation process and outcomes.

## Conclusion

FUEDs represent a vulnerable population multiply affected by medical, psychological, social and substance-use problems accounting for a disproportionally high number of ED consultations. CM intervention tailored to this population has been found to be generally effective in reducing ED overcrowding and improving FUEDs’ quality of life [3, 12–15]. There is, however, very limited knowledge about how to translate and implement such an intervention on a large scale to diverse clinical setting, including community hospitals and non-academic centers. In response, this research project aims to implement the CM intervention in several hospitals in French-speaking Switzerland while evaluating both implementation and clinical outcomes, thereby providing key insights into the mechanisms and processes for disseminating and implementing this intervention into broader practice.

## Abbreviations

CM: Case management
ED: Emergency department
FUED: Frequent users of the emergency department
